**Fig. 4 Fig4:**
[figure not shown]
PATHWEIGH clinic flow

**Table 2 Tab2:** Key components of PATHWEIGH and PATHWEIGH implementation strategies

***PATHWEIGH is a weight management care path built into Epic.*** It includes: • Weight-prioritized visit type: Defines the scope of the visit for the patient and provider. • Time-efficient documentation and data capture: Patient questionnaire completed prior to the visit captures history around weight gain and barriers to weight loss that can guide the patient-clinician conversation and treatment plan. • Clinical decision support: SmartSet in Epic suggests weight loss approach(es) based on patient BMI and preferences according to the Obesity Society guidelines [32]. • Tracking: Displays progress with weight loss and weight loss maintenance during patient visits to guide the patient-clinician conversation and evolving treatment plan over time. • Diagnosis and billing: Tool in Epic automatically adds the diagnosis of overweight (for BMI 25-29.9 kg/m^2^) or obesity (for BMI> 30 kg/m^2^) and links the most common weight-related co-morbidities (according to the Center for Medicare and Medicaid Services) to ensure adequate provider reimbursement.	
***PATHWEIGH implementation strategies*** include: • Practice facilitation: Practice facilitators drive implementation efforts by working with practice-selected Practice Champions, engaging leadership in goal setting and monitoring along system and practice goals, and utilizing quality improvement techniques for supporting adoption, implementation, and management of PATHWEIGH. • Clinician education: Online e-learning module on evidence-based weight management treatment which includes 2 credits of continuing medical education. • Consultation support: built-in to Epic consultation support for clinicians by request; built-in to Epic availability of UpToDate, a subscription-based clinical reference.	

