#### Clinician workflow

To optimize efficiency and guide care, health care providers are encouraged to use the PATHWEIGH weight management SmartSet in Epic. A SmartSet is a documentation template used in the ambulatory setting comprised of a group of orders and other elements, such as notes, chief complaints, medications, and levels of service charges, that are commonly used together to document a specific type of visit. This SmartSet addresses the following.
Diagnosing overweight or obese patients with a BMI > 25 kg/m^2^ or > 30 kg/m^2^, respectively, recognizing these as bona fide disease states [6]Linking diagnoses for weight-related comorbidities to facilitate reimbursementPre-populating information from the patient weight management questionnaire to serve as documentation and to guide the clinician-patient discussion, and flagging weight management strategies based on guidelines from the Obesity Society [32], specifically, the discussion of lifestyle change for patients with BMI ≥ 25 kg/m^2^, consideration of medications impacting obesity as well as anti-obesity medication at BMI ≥ 30 kg/m^2^ (or BMI ≥ 27 kg/m^2^ with weight-related comorbidities) and consideration of bariatric surgery for BMI ≥ 40 kg/m^2^ (or BMI ≥35 kg/m^2^ with weight-related comorbidities)Providing options for orders that include laboratory testing, referrals, or procedures

Behavioral health professionals work alongside many of the primary care providers and are encouraged adjuncts to facilitate weight loss. Use of the PATHWEIGH tools is entirely optional for clinicians. Use may be deployed by the clinicians in advance of the visit or if they or the patient spontaneously decides to prioritize weight management. The process strongly encourages regular follow-up (usually at 4–6 week intervals and more often initially). A key advantage is that the clinician is the patient’s regular provider and will have an ongoing relationship with the patient over time and can safely manage or discontinue medications or other issues for weight-related comorbidities.

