### Aim 2: Identify patient, provider, and clinic-level predictors that are associated with weight loss and weight loss maintenance

#### Outcomes and measures

Patient-level predictors will be captured from the EMR for each visit. Potential patient-level moderators will include age, sex, race/ethnicity, insurance status, baseline BMI, baseline use of medication that may contribute to weight gain, and score > 9 on Patient Health Questionnaire-8 or -9 (PHQ8, PHQ9), or Generalized Anxiety Disorder-7 (GAD7). Patient-level mediators will include treatment prescribed, in particular prescription of anti-obesity medication and performance of an endoscopic or surgical procedure with bariatrics. Provider-level predictors that can be obtained from EMR include provider age, sex, years in practice, and percent time performing clinical duties. Practice-level predictors include patient and provider number and demographics for each, as well as payor mix.

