#### Analysis

Moderation will be evaluated by including an interaction term between the treatment variable and possible moderating variables in the outcome mixed effects regression models used in Aim 1. A significant interaction effect will conclude that the considered variable moderates the effect of PATHWEIGH on the outcome. Mediation analysis will be conducted using the multi-level modeling framework to account for clustering within clinics and providers [45, 46]. Clinic- and provider-level mediators will be restricted to those that can be collected from EMR in both the control and intervention phases. Specifically, we will fit two models: (1) a mediator model to describe the effect of the treatment on the mediator, and (2) an outcomes model to describe the effect of the mediator on the outcome, adjusting for the treatment. Additionally, to be considered a mediator, change in the mediator variable must occur prior to or during the period of patient-level change. Both models will be adjusted for relevant patient-, provider-, and clinic-level variables. The outcomes model will additionally adjust for a time effect to account for temporal effects in the stepped wedge design. These models will be adjusted to include the appropriate random effects and variables based on the level of the considered mediator variable (i.e., patient, provider, clinic). The mediation effect will be summarized as the product of the treatment coefficient from the mediator model and the mediator coefficient from the outcomes model. We will test the null hypothesis that this product is equal to zero, and a statistically significant result will indicate that there is strong evidence that the effect of the treatment on the outcome is mediated by the considered variable. If necessary, we will explore more complex multi-level structural equation models [47].

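### The Aim 2 timing rule lets a prescription or procedure made during the weight change count as its mediator, so treatment that responds to weight can bias the mediation product in either direction

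*Protocol article*

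**What the plan says.** The Analysis text under Aim 2 sets one condition on timing: "to be considered a mediator, change in the mediator variable must occur prior to or during the period of patient-level change". Two models are fitted, one for the mediator and one for the outcome. Mediation is summarised as the "product of the treatment coefficient from the mediator model and the mediator coefficient from the outcomes model", and a product significantly different from zero is taken as strong evidence of mediation, with no condition on its sign. Both models adjust for patient, provider and clinic variables judged relevant. The outcomes model also adjusts for a time effect. More complex structural equation models are possible if needed.

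The Outcomes and measures text under Aim 2 names the mediators: "Patient-level mediators will include treatment prescribed, in particular prescription of anti-obesity medication and performance of an endoscopic or surgical procedure with bariatrics".

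Two descriptions of the intervention bear on this. The tracking component in Table 2 "Displays progress with weight loss and weight loss maintenance during patient visits to guide the patient-clinician conversation and evolving treatment plan over time". Under Clinician workflow, "The process strongly encourages regular follow-up", "usually at 4–6 week intervals and more often initially".

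The primary outcome concerns weight from baseline to 6 months. The Aim 1 model uses weights recorded up to about 9 months.

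**The concern.** A timing condition in a mediation analysis should ensure that the mediator comes before the outcome it is said to cause. Allowing change during the outcome period gives that up. If a drug is first prescribed at month 5, five sixths of a 0–6 month change has already happened and cannot be due to it. That earlier change may have influenced the decision to prescribe.

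The risk is specific to this trial. The named mediators are clinical decisions that can respond to weight, and the intervention is built to show weight progress when those decisions are made. No passage commits to a lag, or to adjustment for weight recorded before the mediator. The mediator coefficient can then mix the effect of treatment with the reason for giving it.

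At stake is the mediation part of Hypothesis II, that is, which treatments carry any PATHWEIGH effect. An effective treatment could appear to carry little or none of it, an ineffective one could appear to be a mediator, or the mediated share could be exaggerated.

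**Working it through.** **1. The plan's own scale.** The article gives no figure for mediation. Its sample-size figures supply N and the outcome SD, so I reproduced those first.
- N = 57 × 120 = 6840.
- Stepped-wedge variance by the Hussey–Hughes formula, with I = 57 clinics (20/18/19), T = 4 periods and 30 patients per clinic-period: σ² = (1 − ICC)/30, τ² = ICC, and Var = Iσ²(σ² + Tτ²) / [(IU − W)σ² + (U² + ITU − TW − IV)τ²].
- U = 20·3 + 18·2 + 19·1 = 115; W = 20² + 38² + 57² = 5093; V = 20·9 + 18·4 + 19·1 = 271.
- ICC 0.02: Var = 0.2098/(1462 × 0.03267 + 3626 × 0.02) = 0.001744. The detectable effect is 2.80 × 0.0418 = 0.117 (stated 0.118). ICC 0.05 gives 0.120 (stated 0.121).
- 0.118 × 10.7 = 1.26 kg and 0.121 × 10.7 = 1.29 kg, as stated. The SD of 10.7 kg is carried forward.

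**2. Treatment decisions inside the window.** Six months is about 26 weeks. 26/6 = 4.3 and 26/4 = 6.5, so patients following the encouraged schedule have about four to six follow-up visits at which treatment could respond to weight.

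**3. Simulation under assumptions.** None of these inputs is in the documents except the SD and the visit interval:
- visits every 5 weeks in both conditions, all attended;
- 5% prescribing per visit under SOC, odds doubled under PATHWEIGH;
- between-patient slopes set so that the 6-month change has SD 10.7 kg;
- mediator M = any prescription before 6 months (ever/never).

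Estimate = a × b, where a is the difference in P(M) between conditions and b is the coefficient of M when weight change is regressed on condition and M. Truth = drug effect per month × difference in mean months on drug. The odds ratio (OR) is per SD of poorer progress.

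Drug effect -1.0 kg/month:

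| OR | P(M) SOC / PATHWEIGH | b (kg) | a × b (kg) | Truth (kg) |
|---|---|---|---|---|
| 1.00 | 0.26 / 0.45 | -3.44 | -0.65 | -0.69 |
| 1.22 | 0.26 / 0.45 | -1.30 | -0.24 | -0.68 |
| 1.35 | 0.26 / 0.45 | -0.32 | -0.06 | -0.68 |
| 1.49 | 0.27 / 0.45 | +0.79 | +0.14 | -0.68 |
| 2.72 | 0.31 / 0.47 | +5.42 | +0.87 | -0.66 |

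For example, at OR 1.00: (0.45 − 0.26) × (−3.44) = −0.65.

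**4. Varying the assumptions.**
- Drug effect -0.5 kg/month: sign reversed from OR 1.22. Drug effect -1.5: about zero at OR 1.65, reversed at 2.01.
- No drug effect: a × b = +0.40 kg at OR 1.22, with b at about z = 7.8 for N = 6840 (clustering ignored). That is false mediation.
- Less persistent slopes (SD 5 kg at 6 months), drug -1.0: -0.64, -0.44, -0.21 and +0.04 kg at OR 1.00, 1.22, 1.65 and 2.72.
- Opposite direction (OR 0.82 and 0.61): -1.05 against a truth of -0.69, and -1.65 against -0.74, so overstated 1.5 and 2.3 times.
- Weights to 9 months with time-by-condition and time-by-mediator terms, drug -1.0: -0.78, -0.18 and +0.16 kg at OR 1.00, 1.35 and 1.65.

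**5. Mediator fixed at the index visit**, drug -1.0: a × b is -0.22 to -0.23 kg against a true index-visit effect of -0.26 to -0.28 kg, for OR 1.0 to 2.7. With no drug effect, b lies between -0.06 and 0.07. Index-visit treatment made up about 20% of prescriptions by 6 months in the 9-month version.

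**The case against.** The strongest reply is that the documents do not describe escalation for poor progress. A reader might infer that PATHWEIGH steps up treatment in non-responders, and hence that the planned analysis will cancel or reverse the mediated effect. The text does not support that. Progress is said to inform an evolving plan, without direction. The only decision rule given, the SmartSet flags under Clinician workflow, works on BMI and comorbidity, and use of the tools is optional. This stands.

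Second, the timing sentence is a necessary condition, not a coding rule. Patient-level predictors are captured at each visit, random effects are to suit the level of the mediator, and earlier weight could be among the relevant covariates. Coding matters. Under a separate set of assumptions (slope SD 0.8 kg/month, drug effect -0.8 kg/month, truth about -0.7 kg), ever/never coding with full attendance gave +0.24 kg. Attendance of 30% and 50% per visit slot gave -0.11 kg, and a time-varying mediator with patient intercepts gave -0.40 kg. So reversal depends on choices the article does not fix, but attenuation remained in all three.

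Third, the 4–6 week schedule belongs to PATHWEIGH, and the Aim 1 Analysis text itself warns that some patients may have no recorded weight within 6 months. Fewer interim weights mean less feedback. This also stands.

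None of this removes the point. The article states a rule that admits treatment given in response to the outcome, and nothing in it commits to correcting for that. This is a stated rule, not a detail left to an analysis plan.

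**Conclusion.** The point holds as a risk of bias of unknown direction and size. The rule allows a mediator to respond to weight change already counted in the outcome, and the named mediators and the tracking feature make such feedback plausible. Moderate dependence is enough to matter under the assumptions shown: at OR 1.22 per SD of poorer progress, about two thirds of a -0.68 kg effect is lost (0.24/0.68 = 0.35 remains). Reversal needs stronger dependence, a weaker drug effect or persistent patient slopes. Dependence on good progress inflates the product instead.

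All these figures rest on assumed prescribing rates, drug effects, attendance and ever/never coding. They show what can happen and do not forecast this trial's result. The primary comparison, the weight-maintenance comparison and the sample size are unaffected. The rule should be changed before the mediation models are run.

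**What to change.** Delete *or during* from the timing rule and require the mediator change to precede the weights it is used to explain. Then specify one of:

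- (a) treatment ordered at the index visit as the mediator; or
- (b) a time-varying or sequential-landmark mediator, with only weights recorded after the prescription or procedure as outcome, adjusted for the last weight recorded before it.

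Option (b) keeps later prescriptions and procedures in the analysis. A single short window after the index visit would drop most later prescriptions and probably most bariatric procedures.

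Also state that a significant product is interpreted as mediation only when its sign agrees with that of the treatment effect. This guards against reading a reversed product as support. It does not detect attenuation or inflation, so it cannot replace the timing change.

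The cost is somewhat more analysis work and lower precision. Option (a) covers early treatment only. Option (b) relies on the EMR weights that happen to be available, which may be sparse.

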### Sample size

A conservative sample size estimate is 6840 total patients (120 patients per clinic from 57 clinics) that assume a minimum of 30 eligible patients per clinic per year based on the smallest clinic. We present the power calculations assuming an intraclass correlation coefficient (ICC) between 0.02 and 0.05. With this design, we will have 80% power (alpha=0.05, two-sided) to detect a standardized effect size of 0.118 (ICC=0.02) to 0.121 (ICC=0.05). For our primary effectiveness outcomes, we estimate a standard deviation (SD) of 10.1 percentage points for percentage change in weight using our pilot study, and a similar SD estimate of 10.7 for absolute (kg) change in weight. Thus, with 80% power we can detect a mean difference in weight change of 1.19 (ICC=0.02) to 1.22 (ICC=0.05) percentage points between the control and intervention conditions, and a mean difference in absolute weight change of 1.26 kg (ICC=0.02) to 1.29 kg (ICC=0.05).

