### Return on investment

A formal return on investment (ROI) analysis will estimate the cost associated with adopting, implementing, and maintaining the intervention in practices and compare this to the difference in reimbursements before and after implementation in each practice. We will adapt a time-driven activity-based costing questionnaire that we have used in several previous studies [55, 56] for the estimation of the cost of staff time used in delivering the SOC and PATHWEIGH visits (including time of PATHWEIGH consulting obesity certified providers), practice facilitation support, and time clinic staff participate in training. In addition, we will measure the cost of materials provided to patients, hiring costs (if any), and other administrative costs incurred for all aspects of PATHWEIGH. To generalize to other settings, we will use industry average compensation costs for providers and staff to value time-driven costs as well as health system average compensation costs for the ROI analysis. Reimbursement data from the health system billing system will be collected for both the control and intervention period. We will collect clinic-level revenue as well as the Medicare allowed amounts for weight-prioritized visits. In addition, for the system-level ROI, we will obtain total system revenue for those patients that have a weight-prioritized visit in each calendar year. A practice perspective ROI will be calculated comparing the PATHWEIGH implementation cost to the difference in reimbursement for weight-prioritized visits during PATHWEIGH implementation and control periods. A system perspective ROI will compare the PATHWEIGH implementation cost to the difference in annualized revenue for patients with a weight-prioritized visit under the PATHWEIGH and control condition.

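### The Aim 2 mediator model has no calendar-time term, so a secular trend in prescribing or procedures could be read as mediation by PATHWEIGH

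*Protocol article*

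**What the plan says.** Protocol article, Aim 2, Analysis: two models are fitted, one for the effect of treatment on the mediator and one for the effect of the mediator on the outcome given treatment. On covariates the text says "Both models will be adjusted for relevant patient-, provider-, and clinic-level variables". It then singles out one of them: "The outcomes model will additionally adjust for a time effect to account for temporal effects in the stepped wedge design". The mediation effect is the treatment coefficient of the first model times the mediator coefficient of the second, and a significant product is to be read as strong evidence of mediation.

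Aim 2, Outcomes and measures: the patient-level mediators are treatments prescribed, in particular "prescription of anti-obesity medication and performance of an endoscopic or surgical procedure with bariatrics".

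Aim 1, Analysis: the primary model carries calendar time as four categorical one-year periods, in order to handle temporal trends.

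Return on investment: the cost of the intervention is estimated, and the plan is to "compare this to the difference in reimbursements before and after implementation in each practice". The practice and system versions contrast PATHWEIGH with control periods or conditions. No time adjustment is named.

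**The concern.** All clinics start in control and cross over in yearly steps, so treatment and calendar time are correlated by design. The protocol recognises this in Aim 1 and in the Aim 2 outcomes model. The mediator model supplies the other half of the tested product and is left without the term. The omission is a stated contrast: after listing what both models share, the text gives the time effect to the outcomes model as an addition.

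Adjusting the outcomes model does not repair the product. Write a for the true treatment effect on the mediator, b for the mediator effect on weight, d for the yearly drift in the mediator, and L for the years of drift absorbed when time is left out. The product then estimates (a + L·d)·b. With a = 0 this is L·d·b, which is non-zero whenever the mediator drifts and affects weight. Upward drift could create apparent mediation, and downward drift could hide real mediation.

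Mediation is part of Hypothesis II, and a conclusion that PATHWEIGH works through prescribing would be among the trial's explanatory findings.

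**Working it through.** **Inputs.** From the protocol: 20, 18 and 19 clinics in sequences 1 to 3 (Table 1); three yearly steps over four years (Design and randomization); "6840 total patients (120 patients per clinic from 57 clinics" and "a minimum of 30 eligible patients per clinic per year" (Sample size). Assumed here: equal patient numbers per clinic-year, linear drift, and the drift rates themselves.

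**1. The plan's own figure.** The protocol states "80% power (alpha=0.05, two-sided) to detect a standardized effect size of 0.118 (ICC=0.02) to 0.121 (ICC=0.05". Hussey-Hughes variance with categorical periods, for I = 57 clinics, T = 4 periods, 30 patients per clinic-period and total variance 1:

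Var = I·s²(s² + T·t²) / [(I·U − W)s² + (U² + I·T·U − T·W − I·V)t²], with t² = ICC and s² = (1 − ICC)/30.

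- U = 20 + 38 + 57 = 115
- W = 20² + 38² + 57² = 5093
- V = 20·9 + 18·4 + 19·1 = 271
- I·U − W = 1462, and the multiplier of t² is 3626

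ICC 0.02: Var = 0.20979/120.28 = 0.001744, SE 0.0418, detectable effect 2.8016 × 0.0418 = 0.117.

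ICC 0.05: Var = 0.41816/227.60 = 0.001837, SE 0.0429, detectable effect 0.120.

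The stated 0.118 and 0.121 are reproduced closely (power 80.7% and 80.6%), and 0.118 × 10.1 = 1.19 points as stated. Without period terms, the same layout gives SE 0.0255 and a detectable effect of about 0.072. The stated power therefore fits a model that adjusts for calendar period.

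**2. How much later intervention time falls.**

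- Control clinic-years: 57, 37, 19 and 0 in years 1 to 4. Mean year (57·1 + 37·2 + 19·3)/113 = 188/113 = 1.66.
- Intervention clinic-years: 0, 20, 38 and 57. Mean year (20·2 + 38·3 + 57·4)/115 = 382/115 = 3.32.
- Pooled gap: 1.66 years.
- Within clinic: sequence 1, year 1 v 3; sequence 2, 1.5 v 3.5; sequence 3, 2 v 4. The gap is exactly 2 years each time.

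A random clinic intercept without time terms gives L = 1.89 (ICC 0.02) to 1.95 (ICC 0.05). The planned multilevel structure therefore does not remove the drift.

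**3. Spurious path = L × d.** At 1 point a year: 1.66 to 2.0 points. At 3 points a year: 4.97 to 6.0 points.

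**4. Effect on the test.** Simulation with a = 0, 1000 runs, 6840 patients, clinic fixed effects, cluster-robust errors and a Sobel test, with period terms always in the outcomes model. Assumed: starting prevalence 5%, b = −4 outcome units, residual SD 10.5, clinic SDs of 2 points (mediator) and 1.8 (outcome), and an outcome trend of −0.2 a year.

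| Drift, points a year | Path, no time term | Mean product | False mediation, no time term | False mediation, with time terms |
|---|---|---|---|---|
| 0 | 0.0 | 0.00 | 5.0% | 5.1% |
| 0.5 | 1.0 | −0.04 | 36.4% | 4.2% |
| 1 | 2.0 | −0.08 | 85.4% | 5.5% |
| 2 | 4.0 | −0.16 | 100% | 5.1% |
| 3 | 6.0 | −0.24 | 100% | 6.4% |

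The Monte Carlo error at 5% is about 0.7 points. A higher starting prevalence softens the result: at 10%, a normal approximation for the treatment-to-mediator coefficient alone gives false rejection of 22 to 23% at 0.5 points a year and 64 to 67% at 1 point.

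**5. Return on investment.** With no PATHWEIGH effect and growth g a year, the before/after ratio for sequence 1 is [(1+g) + (1+g)² + (1+g)³]/3. At g = 3% this is 1.061. Assumed growth of 2, 3, 5 or 10% appears as a gain of about 4, 6, 10 or 21% in every sequence.

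**The case against.** **No trend is documented.** This stands. The Background says that options have multiplied and that medications show improved outcomes. That concerns evidence and availability, not prescribing rates in these clinics. A reader might infer that outside growth will be credited to PATHWEIGH. The documents support only that it would be if it occurs.

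**The text may leave room for time.** Aim 2 says the models will be adapted with suitable random effects and variables. That sentence ties the choice to the level of the mediator (patient, provider or clinic) and does not bring in calendar time. An analysis plan that was not available for this review may already include it, but the article states a rule that points the other way.

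**Clustering is already handled.** Correct. The multilevel framework and random effects are planned for these models, so only the period terms are missing.

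**The return-on-investment text names a quantity, not an estimator.** Largely stands. A condensed article can leave the estimator to a fuller document. Aim 3 plans standardized Medicare rates, and the return-on-investment section collects Medicare allowed amounts; both limit price drift. What remains exposed is growth in visit volume and in actual clinic or system revenue. The percentages in step 5 are shares of baseline reimbursement, not of the return, because implementation cost is not given.

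**An atypical first control year.** Because extraction starts in March 2020, a reader might infer that the first control year was unusual. The protocol mentions COVID-19 only as a health risk and does not describe that year's prescribing or reimbursement, so the point does not rest on this.

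**Conclusion.** The mediation plan is wrong as written. Its treatment-to-mediator coefficient is confounded with calendar time, and nothing else in the article repairs this. The gap of 2 years within clinic (1.66 pooled) is design arithmetic, given equal weight per clinic-year. The resulting bias is conditional: about 2 to 6 points under an assumed linear drift of 1 to 3 points a year, and none without drift. The spurious mediated effect on weight is small in the simulation (0.04 to 0.24 outcome units), but the plan interprets significance, and that is where the error appears.

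A reader might infer that the trial's main result is compromised. It is not: the primary model contains the four calendar years, moderation reuses the Aim 1 models, and the stated power is reproduced with period effects. The return-on-investment point is secondary and softer.

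**What to change.** State in Aim 2, Analysis that the mediator model and the outcomes model both include the same four categorical calendar-year terms as the Aim 1 model.

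For return on investment, where actual revenue or visit volume enters, estimate the reimbursement difference from clinic-by-period data with calendar-period effects, so that clinics not yet crossed over serve as concurrent controls, and carry that difference into the calculation.

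Neither change needs new data or alters the design; both are changes of wording. The cost is wider intervals. In the layout of step 1, the standard error of the treatment coefficient rises from about 0.0255 to 0.0418 at ICC 0.02 (a factor of 1.64) and to 0.0429 at ICC 0.05 (1.68). How much of this reaches the interval for the product depends on how precisely the mediator-to-weight coefficient is estimated. The Aim 1 model already pays this price, and the narrower interval is valid only if there is no drift.

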For the primary analysis, although the parameter of interest is weight change at 6 months, weight collected from baseline to approximately 9 months post-baseline for the individual patient will be included in the primary analysis because patients may not have visits with recorded weight within the 6-month time frame. The mixed model will include random intercepts for patient, provider, and clinic, along with fixed effects for time and intervention condition. The time effects are two-fold: (i) calendar time, divided into four 1-year periods and included as a categorical variable to flexibly model its effect on the outcome and account for temporal trends, and (ii) individual patient time, included as a continuous variable (i.e., time from baseline) to accommodate varying visit times determined by each patient’s visit schedule. The intervention condition variable will be a binary indicator that is equal to zero if the patient’s index visit occurs at a clinic when it is in the control condition and becomes equal to 1 when the patient has an index visit at a clinic after it has crossed into the intervention condition. Patient-, provider-, and practice-level covariates will be included in models if deemed to be potential confounders in univariate models. An additional fixed effect for the interaction between patient time and intervention condition will be used to estimate the parameters of primary interest, i.e., the difference in change in outcomes over time between the intervention and control conditions. The primary analysis will test the null hypothesis that the interaction effect coefficient is equal to zero to determine whether there is a significant difference in weight change between the PATHWEIGH and SOC conditions. Using the model, we will report the mean weight change in the control and intervention groups and their difference at 6 months, with corresponding 95% confidence intervals and *p* values.

To examine the secondary binary outcomes of weight maintenance (defined as < 10% weight gain at 12 and 18 months), we will use generalized linear mixed models. Since this analysis will involve a single outcome per patient, the model will only include a random intercept for provider and clinic. The test of intervention effectiveness will be captured by the fixed effect term for the intervention condition.

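### The raw product of coefficients is an indirect effect on the outcome scale only if both models are linear, yet the named mediators are yes/no and maintenance is binary

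*Protocol article*

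**What the plan says.** The protocol article, under Evaluation, Aim 2, Outcomes and measures, names the mediators: "Patient-level mediators will include treatment prescribed, in particular prescription of anti-obesity medication and performance of an endoscopic or surgical procedure with bariatrics". Each is naturally recorded as present or absent.

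Under Aim 2, Analysis, two models are to be fitted. One is "a mediator model to describe the effect of the treatment on the mediator"; the other relates the mediator to the outcome, adjusting for treatment. The setting is given as follows: "Mediation analysis will be conducted using the multi-level modeling framework to account for clustering within clinics and providers". The mediation effect is then "summarized as the product of the treatment coefficient from the mediator model and the mediator coefficient from the outcomes model", and the inference is: "We will test the null hypothesis that this product is equal to zero". No link function is named for either model, and no variant of the rule is given for a binary mediator or a binary outcome. A fallback is mentioned: "If necessary, we will explore more complex multi-level structural equation models".

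Aim 2 covers both weight loss and its maintenance. Under Aim 1, the primary outcome is weight in kg at 6 months. Maintenance at 12 and 18 months is binary, and for it the protocol says "we will use generalized linear mixed models".

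**The concern.** A product of coefficients is the effect carried by the mediator, on the outcome's own scale, when both models are linear. With a binary mediator and a non-linear mediator model, the first factor is on the link scale (log-odds under a logit) while the second is in kg. The product then has no reading as kilograms lost through prescribing or procedures. With a binary outcome on a logit scale, the second factor is itself a log odds ratio.

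The size and interval reported for each mediator are at stake. A reader who sets such a product beside the total weight difference, or beside the product for another mediator, would be comparing quantities on different scales. Log odds ratios are large relative to risk differences when the mediator is rare, so rare mediators would look more important than they are.

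**Working it through.** **The plan's own figures.** The protocol gives no figure for mediation, so none can be reproduced. The yardstick used below is the detectable total difference in the Sample size section: 0.118 × 10.7 = 1.26 kg and 0.121 × 10.7 = 1.295 kg, against 1.26 to 1.29 kg stated.

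**Weight outcome: formulas.** Let p0 and p1 be the mediator probabilities under SOC and PATHWEIGH. Let b be the mediator coefficient in kg, read as its effect on 6-month weight change, in a linear outcomes model without a treatment-by-mediator interaction.

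- Indirect effect in kg: b × (p1 − p0).
- Product with an identity-link mediator model: b × (p1 − p0), so the factor is 1.
- Product with a logistic mediator model: b × [logit(p1) − logit(p0)].
- Ratio of the logistic product to the indirect effect: [logit(p1) − logit(p0)] / (p1 − p0). It does not depend on b.

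The slope of the logit is 1/[p(1 − p)], which is never below 4, so the ratio is at least 4. It has no upper limit as the mediator becomes rare.

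**Weight outcome: numbers.** The protocol gives no mediator frequencies for the trial population and no mediator effect. The rates and b = −3 kg are assumptions.

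| p0 to p1 | log OR | p1 − p0 | ratio | logistic product | indirect effect (kg) |
|---|---|---|---|---|---|
| 20% to 35% | 0.767 | 0.15 | 5.1 | −2.3 | −0.45 |
| 10% to 20% | 0.811 | 0.10 | 8.1 | −2.4 | −0.30 |
| 5% to 10% | 0.747 | 0.05 | 14.9 | −2.2 | −0.15 |
| 2% to 5% | 0.947 | 0.03 | 31.6 | −2.8 | −0.09 |

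All four logistic products are larger in size than 1.26 to 1.29. At 1% to 2% the ratio is 0.703 / 0.01 = 70. Clustering is left out here; conditional log odds ratios from a mixed model would be slightly larger.

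**Comparison across mediators.** Assume b = −5 kg for each of two mediators, both with logistic models.

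- Rare path, 1% to 2%: product −3.52, indirect effect −0.05 kg.
- Common path, 20% to 30%: product −2.69, indirect effect −0.50 kg.

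The path that carries one tenth of the weight loss has the larger product.

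**Maintenance outcome.** With a logit outcomes model, b is a log odds ratio. A linear mediator model gives risk difference × log odds ratio; a logistic one gives log odds ratio × log odds ratio. Neither is a difference in the probability of maintenance.

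**The test.** The logit is strictly increasing, so its treatment coefficient is zero exactly when p1 = p0. The null of a zero product is therefore the same on either scale. A simulation used 3420 patients per group, SD 10.7 kg, no clustering and 1000 runs per setting. It compared delta-method tests of the logistic product and the risk-difference product:

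| setting | logistic | risk difference |
|---|---|---|
| 5% to 5%, b = −5 (no treatment effect on mediator) | 0.045 | 0.045 |
| 5% to 8%, b = 0 (no mediator effect) | 0.035 | 0.035 |
| 5% to 8%, b = −5 (true mediation) | 0.998 | 0.998 |

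In the last setting the mean products were −2.53 and −0.15. The test decisions agree; the sizes do not.

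**The case against.** The strongest reply is that the protocol never says the mediator model is logistic. The generalized linear mixed models are named for the Aim 1 maintenance outcomes, not for mediators, and no link is given there either. A linear multilevel mediator model fits the text equally well and makes the product correct in kg for the weight outcome. A link is also a detail that a condensed article may leave to an analysis plan. The only inference announced is the zero-product test, which is sound under either link. The aim is to identify predictors: no proportion mediated, ranking of mediators or comparison with the total effect is planned. Clinic- and provider-level mediators need not be binary.

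Much of this stands, and it rules out three stronger readings that a reader might infer:

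- **That the planned quantity is log-odds times kilograms.** This is conditional on a logit link, which the document does not state.
- **That the mediation test is invalid.** It is not, as shown above.
- **That mediation will be overstated by a known multiple, with intervals that miss the truth.** Any multiple rests on assumed rates and the assumed logit. Scoring a log-odds interval against a kg quantity only restates those assumptions.

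The claim that this is merely omitted detail does not fully succeed. The protocol states a summary rule and applies it to mediators it names as yes/no. Choosing an identity link for the mediator does not rescue the maintenance outcome under the usual logit. The structural equation option comes with no trigger and no rescaling rule. The plan also commits to the product as the summary of the effect, so its scale matters even if no ranking is announced.

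**Conclusion.** The point holds as a conditional defect in a stated rule. For the weight outcome with a yes/no mediator, the product is the indirect effect in kg if the mediator model has an identity link. If that model is logistic, the product is too large by a factor of at least 4, and by about 5 to 32 across the assumed rates tabulated. The kg figures also assume a linear outcomes model without a treatment-by-mediator interaction. For binary maintenance under the usual logit link, the product is not on the probability scale whichever link the mediator model uses.

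The reported size, its confidence interval and any comparison across mediators or with the total effect are affected. The zero-product test is not. The matter is confined to Aim 2 and leaves the primary analysis untouched.

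**What to change.** In Aim 2, Analysis, state the link of each model and limit the raw product to cases where both models are linear. For a binary mediator or a binary outcome, report the average indirect effect by standardisation from the same two multilevel models. That is the mean predicted outcome with the mediator distributed as under PATHWEIGH minus the mean with it distributed as under SOC, with treatment held fixed in the outcomes model. For weight without a treatment-by-mediator interaction, this reduces to the mediator coefficient times the risk difference in the mediator.

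Give the result in kg for weight and in percentage points for maintenance, beside the total effect on the same scale. Use an interval that respects clustering, such as a bootstrap that resamples clinics. The zero-product test can stay.

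No new data or models are needed. The cost is a change of wording, standard code and the computing time of the bootstrap.
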